### Outcomes and participant timeline

2.5.

The outcome indicators will be extracted from the CRF table after the patient is discharged and then uploaded to the online web-based database. Confirmation of outcome data will be undertaken with an additional sign-off by the site's principal investigator for each participant.

#### Coprimary outcomes

2.5.1.

Thoracic-related complications include pleural effusion, pneumothorax, and pneumonia diagnosed on chest radiograph.

Medical expenses during hospitalization are the total expenses recorded in the hospitalization electronic system, all of which are the original expenses before insurance reimbursement and are denominated in RMB.

#### Secondary outcomes

2.5.2.

The length of hospital stay is defined as a secondary outcome indicator, as it is a measure of the time cost for patients and their families.

The surgical duration affects the early recovery of children to a certain extent; therefore, it is defined as a secondary endpoint event, especially considering that this study was conducted using conventional tracheal intubation rather than tubeless techniques. Indeed, we emphasize that the long duration of the surgery cannot directly evaluate the quality of the surgical method.

#### Participant timeline

2.5.3.

The time schedule of enrollment, interventions, and assessments are described in detail in a schematic diagram (Table 1).

**Table 1 T1:** Schedule of Enrolment, allocation, intervention and close-out.

Specific procedure	Enrolment	Allocation		Intervention					Close-out
Time point	D0	D0	D1	D2	D3	D4	Every day	DN	
Eligibility screen	●								
Informed consent	●								
Block randomization		●							
Preoperative examination			●						
Undergo surgery				●					
Analgesic pump				●	●				
Chest radiograph					●			●	
VAS score						●	●	●	
Walking experiment								●	
Data management									●

● The green dot indicates that this project will take place at this time point.

### Sample size and recruitment

2.6.

Medical expense during hospitalization is the primary outcome indicator of this study because it can objectively evaluate the financial burden of the patient's family. Based on our retrospective research data on surgeries over the past three years, the average cost of the TNP group was 30,250 RMB, while the average cost of the SINTNP group was 28,157 RMB. The standard deviation will be set as 2,000, and the superiority margin will be set as 1,500. The sample size will be calculated to require at least 141 children in each group.

The proportion of thoracic-related complications was approximately 9.6% in SINTNP and 13.6% in nonthoracoscopic-assisted Nuss surgery with double incision. The sample size calculation requires over 3,000 people per group according to the proportion of thoracic-related complications, and currently, we are unable to recruit so many patients. We will truthfully describe this recruitment-related limitation in the officially published article. Considering a 10% to 15% withdrawal and dropout rate, each group will ultimately include 160 children.

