#### Primary objectives

2.1.1.

The coprimary objectives of the study are to assess differences in thoracic-related complications and medical expenses during hospitalization of PE patients undergoing SINTNP or TNP.

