### Interventions

2.4.

After randomization into two groups, the enrolled patients will undergo routine preoperative preparation, including blood biochemical tests, and antibiotics will be administered once 30 min before surgery. All patients will undergo general anesthesia under tracheal intubation and receive T4 and T5 paravertebral nerve block. The SINTNP group will undergo left-side single-incision nonthoracoscopic-assisted Nuss surgery in accordance with our previous report (10). The TNP group will undergo thoracoscopic-assisted Nuss surgery with bilateral incisions, with the endoscopic observation hole on the right side. We need to emphasize that any child who requires the use of two bars during surgery will be withdrawn from the study cohort. After postoperative resuscitation, the patient will return to the ward and use a pain pump within 48 h after surgery.

One day after the surgery, chest radiograph bedside ward examination will be conducted. Starting from the second day after the surgery, a VAS pain score will be collected every morning. Those with a score of three or less will undergo the 100-meter walking experiment. Those who can successfully complete the 100-meter walking experiment independently and do not report any special discomfort will undergo chest radiograph examination. Those who had no obvious pneumothorax, pleural effusion, or steel plate displacement were discharged the next morning. If the child has a clear tendency toward plate allergy, such as extensive redness and swelling of the anterior chest wall skin or poor wound healing, such as incision suppuration, the patient will withdraw from the study. Their data will not be included in the analysis of pre-protocol set but will be truthfully reported and analyzed in the final research report of full analysis set.

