In the study, we only compare SINTNP to TNP and do not focus on the comparison between double incision non-thoracoscopic Nuss Procedure (DINTNP) to TNP. This is mainly due to two reasons. Firstly, because TNP requires two incisions, if we also use two incisions in non-thoracoscopy assisted Nuss surgery, then we do not utilize the advantages of non-thoracoscopy assisted surgery. Theoretically, DINTNP takes longer and has more injuries compared with single incision. The other reason is that our previous research has confirmed that the SINTNP will not increase the probability of postoperative bar displacement compared with the DINTNP. SINTNP is safe and reliable. Therefore, the current research setup is more in line with clinical scenarios.

Hence, we conducted this multicenter randomized controlled study. We believe that the results of this study are generalizable to other populations or healthcare settings. The learning curve of Nuss procedure is not long. Most thoracic surgeons can master this technique skillfully after a 10-procedure proctoring period (17). Non Thoracoscopy assisted single incision surgery has been carried out in many institutions. In addition, perioperative evaluation and nursing methods are also very common. The vast majority of institutions can perform preoperative CT, lung function, and echocardiography on children. Previous literature did not report significant cross regional or racial differences in the prognosis of Nuss surgery. Therefore, we believe that the results study can be widely generalized.

It is worth noting that although all researchers have undergone standardized training and each center's research will strictly follow the protocol. The potential bias in patient recruitment, protocol implementation, and data collection in multicenter studies cannot be completely avoided. We would like to confirm that for children with pectus excavatum who undergo their first surgery and need to use only one bar, the single-incision nonthoracoscopic Nuss procedure is sufficient. Other methods for ensuring safety, such as thoracoscopy or bilateral incision, are unnecessary.

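### Section 2.6 makes medical expense the only primary outcome while the rest of the protocol keeps thoracic complications co-primary, and it plans complications on a rate from a procedure that is not the control arm

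*Protocol article*

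**What the plan says.** **Hierarchy.** Section 2.1.1 reads: "The coprimary objectives of the study are to assess differences in thoracic-related complications and medical expenses during hospitalization". The abstract and 2.5.1 likewise list both endpoints as co-primary. Section 2.6 reads: "Medical expense during hospitalization is the primary outcome indicator of this study".

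**Sizing.** Section 2.6 derives 141 per group from expense (means of 30,250 and 28,157 RMB, SD 2,000, superiority margin 1,500). After an allowance of 10% to 15% for dropout, "each group will ultimately include 160 children".

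**Complications.** Section 2.6 gives the planning rates: "The proportion of thoracic-related complications was approximately 9.6% in SINTNP and 13.6% in nonthoracoscopic-assisted Nuss surgery with double incision". It continues: "The sample size calculation requires over 3,000 people per group according to the proportion of thoracic-related complications". It concedes that so many patients cannot be recruited and promises to report this limitation. No alpha, sidedness, power or margin is stated for this calculation.

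**Control arm.** Section 2.4: "The TNP group will undergo thoracoscopic-assisted Nuss surgery with bilateral incisions". The Discussion adds: "we only compare SINTNP to TNP and do not focus on the comparison between double incision non-thoracoscopic Nuss Procedure (DINTNP) to TNP".

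**The concern.** Three things in one short section do not fit together.

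- The endpoint hierarchy differs between 2.6 and the rest of the protocol.
- The comparator rate for complications carries the name of a procedure that the Discussion treats as separate from TNP and outside the comparison.
- The required size is far larger than the two printed rates would normally produce.

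What is at stake is the claim that the trial may make about complications. An endpoint called co-primary will be read as confirmatory. With about 160 per group, a nonsignificant difference is the likely result unless the TNP rate is much higher than 13.6%, and it could be read as equal safety. The protocol invites that reading: 2.2 speaks of noninferiority tests although the abstract describes a superiority trial, and the Discussion hopes to show that thoracoscopy is unnecessary.

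**Working it through.** **Inputs.** From 2.6: rates 0.096 and 0.136, difference 0.040; 160 per group; dropout 10% to 15%, which leaves 160 × 0.90 = 144 to 160 × 0.85 = 136. From 2.11: chi-square test. Alpha and power are not stated, so the usual values are tried.

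**1. Expense figure (reproduces).** Difference 30,250 − 28,157 = 2,093; less the margin, 593.

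n = 2 × 2,000² × (1.645 + 0.842)² / 593² = 140.65, so 141.

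The section's expense convention is therefore one-sided 5%, 80% power, with a margin.

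**2. Complications figure (does not reproduce).** Variance term: 0.096 × 0.904 + 0.136 × 0.864 = 0.2043. Then n = (z_alpha + z_power)² × 0.2043 / 0.04².

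| Setting, no margin | n per group |
|---|---|
| one-sided 5%, 80% power | 790 (pooled formula 792) |
| two-sided 5%, 80% power | 1,003 (pooled 1,005) |
| two-sided 5%, 90% power | 1,342 (pooled 1,345) |
| two-sided 5%, 95% power | 1,660 (pooled 1,663) |

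A continuity correction adds about 50 to each. With these two rates and no margin, 3,000 is passed only at extreme settings (two-sided 1%, 99% power: 3,075).

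With a 2-point margin under the expense convention, n = (1.645 + 0.842)² × 0.2043 / (0.04 − 0.02)² = 3,158. No such margin is stated for complications.

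**3. Power at the planned size, if 13.6% applied to TNP.**

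| n per group | two-sided 5% | one-sided 5% |
|---|---|---|
| 136 | 17.6% | 26.9% |
| 141 | 18.1% | 27.5% |
| 160 | 19.9% | 29.9% |

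Exact enumeration of the uncorrected two-sided chi-square test gives 17.6%, 18.1% and 20.2%. With the 2-point margin at one-sided 5%, power is about 13-14%.

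**4. Precision.** 95% half-width for the risk difference: 1.96 × √(0.2043/160) = 7.0 points; 1.96 × √(0.2043/136) = 7.6 points. The planned difference is 4 points.

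**5. Dependence on the missing TNP rate.** SINTNP is held at 9.6%; the TNP rates are assumptions; two-sided 5%.

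| Assumed TNP rate | power at 141 to 160 per group | n per group for 80% power |
|---|---|---|
| 12% | about 10% | 2,625 |
| 13.6% | 18-20% | 1,005 |
| 15% | 28-31% | 580 |
| 18% | 53-59% | 264 |
| 20% | 69-75% | 182 |

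At 136 to 160 per group, 80% power needs a TNP rate of about 21% to 22%.

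**The case against.** **The shortfall is disclosed.** Section 2.6 says that the complications requirement cannot be recruited, bases the size on expense and commits to reporting the limitation. Section 2.1.1 speaks only of assessing differences. This is a fair point on candour, and keeping an imprecise endpoint with a caveat is partly a matter of choice. But disclosure does not settle whether the trial has one primary endpoint or two, and it does not supply a rate for the control arm.

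**The power figure uses the rate under criticism.** This is right. The 18-20% holds only if 13.6% applies to TNP. A reader might take it as the trial's actual power, or take about 1,000 per group as the true requirement. The protocol supports neither, because both move with a TNP rate that it does not give.

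**Over 3,000 may have a sound origin.** This also stands. A 2-point margin under the section's own expense convention gives 3,158, and an unprinted TNP rate below 13.6% would also raise the figure. A reader might infer that the figure is wrong. The supportable statement is that it cannot be obtained from the stated inputs.

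**A both-or-either rule can sit in the analysis plan.** Agreed. A reader might infer that type I error is inflated, or that the trial is bound to fail on a joint criterion. Each inference presumes a decision rule that the protocol does not state and that an analysis plan not shown may fix. Neither is part of this point.

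**The label may be a slip.** Possibly the 13.6% is a TNP rate with the wrong name. Then the label needs correcting, and the power in step 3 applies as it stands.

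**Conclusion.** The point holds in three parts.

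- The endpoint hierarchy in 2.6 contradicts the abstract, 2.1.1 and 2.5.1.
- The 13.6% is labelled as double-incision non-thoracoscopic surgery, which is not the control arm, and no TNP rate appears. As written, one co-primary endpoint has no planning basis for the comparison being tested.
- Over 3,000 per group does not follow from 9.6% and 13.6%. Usual settings give about 790 to 1,345; reaching 3,000 takes an unstated margin or extreme settings.

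On the condition that 13.6% applies to TNP, the endpoint has about 18-20% power (two-sided 5%) or 27-30% (one-sided 5%) with 136 to 160 per group, and an interval nearly twice as wide on each side as the difference sought. Neither sidedness comes near adequate power. Without a TNP rate the true power is unknown; a TNP rate of about 21% to 22% would be needed for 80%.

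The sizing for expense is not affected: its 141 per group reproduces exactly.

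**What to change.** - Make medical expense the single primary endpoint throughout, as 2.6 already says. Change the abstract, 2.1.1 and 2.5.1 to match.
- Move thoracic complications to the leading secondary endpoint, reported as a risk difference with 95% confidence interval. State that no confirmatory claim will be made and that a nonsignificant result will not be taken as equal safety.
- Replace 13.6% with the retrospective TNP rate, or correct the label if the figure already is that rate. If no TNP rate is available, say so.
- Recompute the required size and the power at 160 per group from that rate, and state the alpha, sidedness, power and any margin used.

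**Cost.** No extra patients. The nominal co-primary claim on complications is given up. Section 2.13 rules out changes after publication, so the change needs a dated, openly explained correction and a registry update, preferably before outcome data are seen.

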**Methods:**

This study is a prospective, superiority, multicenter, non-masked, randomized controlled trial that investigates the outcome and hospitalization medical expense of SINTNP compared to TNP for PE. A total of 320 eligible patients according to sample size calculation by retrospective data will be randomly assigned to the SINTNP group or the TNP group at a 1:1 ratio using stratified blocked randomization and the zone length was set as four. Patients aged between 3 and 18 years old for the first surgery and without combination of complex anomalies such as Marfan syndrome and congenital heart disease will be considered for the study. The co-primary endpoint is thoracic related complications and medical expense during hospitalization. Thoracic related complications were defined as pneumothorax, pleural effusion, pneumonia and incision infection. The secondary endpoints include surgery duration and length of hospital stay.

The registration number for this study protocol is ChiCTR230073081 (Chinese Clinical Trial Registry, A Primary Registry of International Clinical Trial Registry Platform, World Health Organization).

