### Trial design and study setting

2.2.

The study is a multicenter, non-masked, randomized controlled trial including patients with PE aged between 3 and 18 years old for the first surgery and without a combination of complex anomalies.

The participants will be randomly assigned to the SINTNP or TNP group with a balance of 1:1. Participants will be allocated as evenly as possible to four hospitals in western China. The sponsor institution was Children's Hospital of Chongqing Medical University. This multicenter study will also be conducted in Chengdu Women and Children's Central Hospital, Chongqing Three Gorges Central Hospital and Qujing Maternal and Child Health Hospital.

Due to objective conditions, the participants in the four centers cannot be completely balanced, but the participants in any center will not exceed 50% of the total number or be less than 15% of the total number. Independent statisticians will perform noninferiority tests for comparisons of SINTNP to TNP.

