### Statistical methods

2.11.

Continuous data will be presented as the means with standard deviations (SDs) or medians with interquartile ranges (IQRs). The Kolmogorov–Smirnov test will be used to evaluate normality. Continuous data will be compared between the two groups by unpaired t test (normal distribution) or the Mann‒Whitney *U*-test (nonnormal distribution). A chi-square test will be used to compare categorical variables between two groups. Pre-protocol analysis (PP) will be performed with data of participants finishing the whole study and intention to treat analysis (ITT) will be used in full analysis set. Inter group analysis across centers were performed to evaluate the influence of bias and the reliability of the overall study.

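### Enrolling 160 per group does not preserve the required 141 at the stated 15% loss: 136 remain, and 160 covers losses only up to 11.9%

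*Protocol article*

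**What the plan says.** Section 2.6 (Sample size and recruitment) sizes the trial on medical expense during hospitalization. From retrospective data, "the average cost of the TNP group was 30,250 RMB, while the average cost of the SINTNP group was 28,157 RMB". It then fixes the other two inputs: "The standard deviation will be set as 2,000, and the superiority margin will be set as 1,500". The result is: "The sample size will be calculated to require at least 141 children in each group". The step from evaluable to enrolled children is: "Considering a 10% to 15% withdrawal and dropout rate, each group will ultimately include 160 children". The Abstract carries the total forward: "A total of 320 eligible patients according to sample size calculation by retrospective data".

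Section 2.6 gives no significance level, sidedness or power for this calculation, and no other section supplies them. Section 2.11 (Statistical methods) says only: "Continuous data will be compared between the two groups by unpaired t test (normal distribution) or the Mann‒Whitney" U-test, without a margin or a side. It plans a per-protocol analysis of children who finish the study and an intention-to-treat analysis in the full analysis set.

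**The concern.** Three figures printed in one section should be linked by simple arithmetic: the evaluable minimum (141), the expected loss (10% to 15%) and the number enrolled (160). They agree at the lower end of the loss range and not at the upper end. A reader who takes section 2.6 at its word will believe that the minimum is protected against 15% loss, and it is not.

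A second, smaller matter is that 141 cannot be interpreted without knowing the level and power it was computed for. Medical expense is the only endpoint that determines the trial's size, since section 2.6 says the complications endpoint would need over 3,000 per group and cannot be met. The level of the margin test changes its power by about ten points, so it is useful for section 2.6 to name it.

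**Working it through.** **Inputs (all from section 2.6; 1:1 allocation from section 2.2)**
- Means 30,250 and 28,157 RMB: difference 2,093 RMB.
- Superiority margin 1,500 RMB: difference beyond the margin 2,093 − 1,500 = 593 RMB.
- Standard deviation 2,000 RMB.
- Evaluable minimum 141 per group; enrolled 160 per group; loss 10% to 15%.
- Level, side and power are not stated, so the range is shown.

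**Step 1: reproduce 141.** Normal approximation, n per group = 2(z_α + z_β)² × 2,000² / 593².
- One-sided 5%, 80% power: 2 × (1.645 + 0.842)² × 4,000,000 / 351,649 = 140.7, so 141. This matches the article.
- One-sided 2.5% (two-sided 5%), 80% power: 178.6, so 179.
- One-sided 5%, 90% power: 194.8, so 195.
- One-sided 2.5% (two-sided 5%), 70% power: 140.4, so 141. This also matches, though 70% is an unusual target.

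**Step 2: from 141 to 160.**
- 10% loss: 160 × 0.90 = 144 remain, above 141. Enrolment needed: 141 / 0.90 = 156.7, so 157.
- 15% loss: 160 × 0.85 = 136 remain, 5 below 141. Enrolment needed: 141 / 0.85 = 165.9, so 166 per group, or 332 in total against 320.
- Cruder add-on at 15%: 141 × 1.15 = 162.2, so 163, still above 160.
- Largest loss that leaves 141: 1 − 141/160 = 11.9%.

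**Step 3: what the shortfall costs.** Power of the test against the 1,500 RMB margin, by the noncentral t distribution:

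| Evaluable per group | One-sided 5% | One-sided 2.5% |
|---|---|---|
| 136 | 78.6% | 68.3% |
| 141 | 79.9% | 69.9% |
| 144 | 80.7% | 70.8% |
| 160 | 84.2% | 75.3% |

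The normal approximation gives values within 0.5 point of these. At one-sided 5%, going from 141 to 136 costs 79.9 − 78.6 = 1.3 points.

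**The case against.** The strongest reply is that 160 is a reasonable compromise inside the stated range. A loss of 10% to 15% implies 157 to 166 enrolled (or 156 to 163 by simple add-on), and 160 lies inside both intervals. The most it can cost is 1.3 points of power. Moreover, not every withdrawal is a loss to the analysis. Section 2.4 keeps children withdrawn for plate allergy or poor wound healing in the full analysis set, and cost is an in-hospital total. If all 160 were analysed, power at one-sided 5% would be about 84%.

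Most of this stands, and it is why the point is minor. It does not remove the mismatch. A number that covers only part of a stated range should not be presented as covering the whole of it. The shortfall applies directly to the per-protocol analysis. For children who turn out to need two bars, section 2.4 says only that they leave the study cohort, without saying whether their data are kept.

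A reader might go further and infer that 141 is wrong, that the trial's power is overstated, or that it has 70% power rather than 80%. The document does not support any of these. It states no power, so there is no figure to overstate. A test of superiority by a margin is naturally one-sided, and 141 is correct for it at 5% with 80% power. The 70% figure requires a margin test at one-sided 2.5%, a level the article never sets. If the section 2.11 test were instead an ordinary two-sided t test of zero difference, power would be no problem: with 136 per group the standard error is 2,000 × √(2/136) = 242.5, and 2,093 / 242.5 is about 8.6. The level and power may also stand in the full protocol or analysis plan, which is not shown.

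**Conclusion.** The inconsistency is certain and needs no assumption: at the stated 15% loss, 160 per group leaves 136 children, 5 below the section's own minimum of 141, and the minimum holds only for losses up to 11.9%. Its consequence is minor: about 1.3 points of power (79.9% to 78.6%), assuming a one-sided 5% test against the 1,500 RMB margin and the article's own means and standard deviation, and mainly in the completers analysis.

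Secondarily, 141 is arithmetically sound. At 80% power it corresponds to a one-sided 5% margin test, and section 2.6 would be clearer if it said so. Only if one-sided 2.5% (two-sided 5%) is intended does the size become a larger matter: the same inputs then need 179 evaluable per group, and 141 gives about 70% power.

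**What to change.** Keep 160 per group and correct the statement in section 2.6 in one of two ways:
- say that 160 preserves 141 evaluable children only for losses up to about 12%; or
- keep the 10% to 15% expectation and say that at 15% loss 136 per group remain, with about 78.6% power (one-sided 5%) in a completers analysis.

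The second is preferable if losses of up to 15% are still expected, because it leaves that expectation unchanged and reports what follows from it.

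In the same place, state that 141 rests on a one-sided 5% test against the 1,500 RMB margin with 80% power, and that the final margin test uses that level. If one-sided 2.5% is intended instead, state that 80% power would need 179 evaluable per group and give about 70% as the power at 141.

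The cost is wording only, with no extra children. Section 3 says the study has not started, so the level can be fixed before any data are seen. Because section 2.13 rules out changes after publication, this is best issued as a clarification of the existing calculation.
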